#### Assessment

Quantitative and qualitative assessments will be performed before the intervention (T0), immediately after the intervention (T1) and at the six months follow-up (T2). Participants will respond to the same electronic form used in Phase 1 of the study at the three evaluation moments (T0, T1 and T2) and after the intervention they will be able to respond subjectively about their adherence to the sessions, frequency of performing formal practices and report if there were unexpected effects (adverse events) in periods T1 and T2 by completing another electronic form [46]. After six months of follow-up, the control group will be offered the intervention (MBHP or ABCT) considered most effective to improve eating behavior (Fig. 2).

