#### Sample size

Sample size estimates indicate that for a 30 % improvement in the primary outcome for groups G1 and G2 and 5 % for group G3 (workshop), with a 95 % bilateral confidence interval and 80 % power, each group will need at least 43 participants. Assuming that 25 % of patients would be lost to follow-up, each group would need 54 patients, with 162 participants in total.

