#### Analyses plan

Descriptive statistics will be used to determine the feasibility, acceptability, and effect of Mindfulness-based and compassion-based interventions. The initial baseline characteristics will be revised visually for an approximate balance between groups. For the sociodemographic questionnaire (including the different surgical procedures performed), absolute and relative frequencies will be calculated for categorical variables, whereas means and standard deviations will be estimated for continuous variables.

Statistical procedures will be performed on an intention-to-treat and/or per-protocol basis. For data tabulation and analysis, Excel 2010 programs and SPSS software version 23.0 for Windows (SPSS Inc.; Chicago, IL, USA) will be used. All variables will be subjected to the Kolmogorov-Smirnov test to verify the normal distribution of data. For initial comparisons between the groups, the unpaired *t*-test (two-tailed) or Mann-Whitney U test (two-tailed) will be used for continuous variables whereas Fisher's exact test (two-tailed) and the chi-square test will be used for categorical variables.

After the intervention, a within- and between-group comparative analysis of the scales will be performed with initial and final data using the paired and unpaired *t*-test (two-tailed) for variables with normal distribution (mean, standard deviation, and 95 *%* confidence interval) and the Mann-Whitney U test (two-tailed) for variables with non-normal distribution. Differences between the initial and final means (Δ) of the study variables will be calculated and a comparative analysis of these means will be performed using the *t*-test for independent samples or the Mann-Whitney U test. Statistical procedures will be performed per protocol based on the intention-to-treat analysis. The number needed to treat (NNT) and the number needed to harm (NNH) will be calculated.

To identify the correlation between the study variables and HADS scales, the MAAS, SCS, MAQoLQII, Rep(eat)-Q, TFEQ-R21, BES, ECR-R-Brazil, silhouette scales, and Pearson's and Spearman's correlation coefficient will be used at three time points. At the end of the study, linear regression analyses will be performed with the total sample using complete cases and stratified by weight gain to assess the mediating effect of the statistical relationship between the study scales in the intervention group.

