The laminates are established from less postoperative weight in the first year, as follows: 1 to 10 % weight regained from 11 to 20 %, etc. The level of significance will be 5 % (*p* < 0.05) in all tests.

The qualitative data will be analyzed using the thematic content analysis technique [47]. The NVivo software (version 12) will be used for this organization and treatment. Data will be treated by lexical coding, thematic analysis, and association between linguistic, paralinguistic, and sociodemographic variables.

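### For scales that fail the normality check, the only test named for the within-group before-after comparison is the Mann-Whitney U test, which is not valid for paired scores

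*Protocol article*

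**What the plan says.** All of this is in the protocol article, Phase 2. Under Analyses plan, a normality check comes first: "All variables will be subjected to the Kolmogorov-Smirnov test to verify the normal distribution of data". The plan then sets out how scores are compared once the programmes end: "a within- and between-group comparative analysis of the scales will be performed with initial and final data". Scales judged normal get a t-test in both its paired and its unpaired form. For the rest the plan names "the Mann-Whitney U test (two-tailed) for variables with non-normal distribution". The paired/unpaired distinction is made for the t-test and not for the rank test.

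The next step in the same section concerns change: "Differences between the initial and final means (Δ) of the study variables will be calculated", and these are compared with the independent-samples t-test or Mann-Whitney U.

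The Assessment section shows that the data are repeated measures: "Participants will respond to the same electronic form used in Phase 1 of the study at the three evaluation moments (T0, T1 and T2"). The significance threshold is common to all tests: "The level of significance will be 5" %.

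No signed-rank, sign, Friedman or other paired rank test is named anywhere in the article.

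**The concern.** Mann-Whitney U compares two independent samples. In a within-group comparison the two samples are the same people at two times. The test ignores that link, so its standard error does not fit the data. If participants who score high before also tend to score high after, the standard error is too large, the p-value is too large and a real change is harder to detect.

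At stake are the within-arm results for any scale routed to the rank test. A scale that passes the normality check gets a proper paired test. If the eating scales split on that check, their within-arm p-values would not be on the same footing. The documents do not show whether such a split will occur.

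**Working it through.** **1. The plan's own figure.** The Sample size section assumes "for a 30 % improvement in the primary outcome for groups G1 and G2 and 5 % for group G3 (workshop"), two-sided 5% and 80% power, and gives 43 per group. Treated as two proportions, with mean proportion 0.175:

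- n = [1.96·√(2·0.175·0.825) + 0.8416·√(0.30·0.70 + 0.05·0.95)]² / 0.25² = (1.053 + 0.427)² / 0.0625 = 35.1, or 36 rounded up.
- With continuity correction: (35.06/4)·[1 + √(1 + 4/(35.06·0.25))]² = 42.7, or 43.

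The 43 reproduces. The present point does not depend on it; it only sets a realistic arm size. The plan enrols 54 per arm and expects 25% loss, and 54 × 0.75 = 40.5, so arms of 40, 43 and 54 were examined.

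**2. Which test applies to which comparison.**

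| Comparison | Normal scale | Non-normal scale | Valid? |
|---|---|---|---|
| Within group, before vs after | paired t | Mann-Whitney U, the only one named | rank test: no |
| Between groups | unpaired t | Mann-Whitney U | yes |
| Between groups, change Δ | independent-samples t | Mann-Whitney U | yes |

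The Δ step compares groups, so it does not supply the missing within-group test.

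**3. Large-sample size of an unpaired test on paired data.** With equal variances σ² and correlation r, the true variance of the mean difference is 2σ²(1 − r)/n, while an unpaired test uses 2σ²/n. Under no change the statistic therefore has standard deviation √(1 − r), and the actual type I error is 2·[1 − Φ(1.96/√(1 − r))].

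- r = 0: 5.0%
- r = 0.3: 1.96/0.837 = 2.34, giving 1.9%
- r = 0.5: 1.96/0.707 = 2.77, giving 0.6%
- r = 0.7: 1.96/0.548 = 3.58, giving 0.03%
- r = −0.3: 8.6%, so the direction reverses if r is negative

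The documents do not give r. All values here are assumptions.

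**4. Simulated type I error, Mann-Whitney on paired skewed scores (nominal 5%).**

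| r (assumed) | Gamma scores, n = 40 | Lognormal, n = 43 | Lognormal, n = 54 |
|---|---|---|---|
| 0.3 | 2.3% | 2.2% | 2.1% |
| 0.5 | 0.8% | 0.8% | 0.6% |
| 0.7 | 0.15% | 0.07% | 0.08% |

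The lognormal results use 10,000 data sets per setting. At r = 0.7 rejections are so rare that another gamma simulation gave 0.03%; 0.2% or less is a fair summary. The signed-rank test stays near 5% throughout (4.6% to 5.0% in the lognormal model at n = 43).

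**5. Simulated power, Mann-Whitney vs signed-rank.**

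| r (assumed) | Gamma, n = 40, 0.4 SD fall | Lognormal, n = 43, 0.3 SD shift on the log scale |
|---|---|---|
| 0.3 | 58% vs 61% | 23% vs 33% |
| 0.5 | 57% vs 75% | 20% vs 43% |
| 0.7 | 59% vs 91% | 14% vs 63% |

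In the gamma model the loss is about 3, 18 and 32 points. In the lognormal model it is about 10, 23 and 49 points. It depends on both r and the shape of the scores.

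**The case against.** **The trial's question is between arms.** The aim is to compare the two programmes with usual care and with each other. Those comparisons use two-sample tests on different people, and Mann-Whitney is valid there, including for Δ. A within-arm p-value cannot separate treatment from time or regression to the mean. This stands. A reader might infer that the error undermines the trial's comparative conclusions; the documents do not support that.

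**The error is in the cautious direction.** With positive r it creates no extra false claims of benefit. This also stands. A reader might infer inflated false positives, but that would need a negative before-after correlation, and nothing in the documents suggests one.

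**The size is conditional.** A reader might infer that every within-arm p-value is badly wrong. That goes too far. The problem arises only for scales that fail the Kolmogorov-Smirnov check, and the documents do not say which, if any, will. At r = 0.3 the gamma model loses only about 3 points of power, and r could be modest over a six-month follow-up.

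**The sentence may be compressed.** This is a journal article, and the paired rank test may have dropped out in the editing; the full protocol or analysis plan is not shown. Mann-Whitney may have been meant for the between-group part only. That is plausible, and it argues against reading the sentence as a deliberate choice to treat pairs as independent. It does not rescue the sentence as printed: one test is attached to both kinds of comparison, while the t-test was carefully split. On the charitable reading, the within-group comparison of non-normal scales is left with no test, and the same clause closes that gap.

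**Conclusion.** The concern holds as an error of stated method with limited reach. As printed, the within-group comparison of a non-normal scale would use a test whose independence assumption the design violates. The conclusion that the test is invalid there needs no assumption beyond the repeated measurement that the article describes.

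The size does rest on assumptions: a positive r, which is not in the documents, and a skewed score. On that basis the actual type I error is about 2% at r = 0.3, 0.8% at r = 0.5 and 0.2% or less at r = 0.7, instead of 5%. The power loss ranges from negligible to severe as r rises. The consequence is missed within-arm change, in a study that seeks preliminary evidence. The randomised between-arm and Δ comparisons are unaffected.

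**What to change.** In the Analyses plan, split the rank test as the t-test is already split. Name the Wilcoxon signed-rank test for within-group comparisons of non-normal scales, or report the paired mean change with a bootstrap 95% confidence interval. Keep Mann-Whitney U only for between-group and Δ comparisons. If the full protocol or analysis plan already says this, correcting the published sentence to match is enough.

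The cost is one clause. It needs no new data, no extra participants and no change of design.

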### Phase 2: clinical trial

#### Trial design

This is a randomized controlled clinical trial of mixed methods with random allocation in three groups: G1 (MBHP + workshops); G2 (ABCT + workshops); and G3 (workshops), with patients who underwent gastroplasty and regained weight from the clinic already mentioned.

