#### Outcomes

The primary outcome will be a change in the eating behavior (TFEQ-21, Rep (eat)-Q, and BES) at all steps. Secondary outcomes will be improved quality of life (M-A QoLQII), increased satisfaction with body image and reduced distortion (BSSA), better weight management (maintenance or weight reduction), increased frequency of physical activity, and monitoring with the surgery team. The explicative variables will be the level of mindfulness (MAAS), self-compassion (SCS-SF), anxiety (HADS), and attachment style (ECR-R).

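### With 25% loss expected, t or Mann-Whitney tests on change scores compare only participants with final data, so the intention-to-treat wording does not protect the group comparison

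*Protocol article*

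**What the plan says.** All places are in Phase 2 of the protocol article.

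- **Sample size** sets the target and the allowance for loss: "with a 95 % bilateral confidence interval and 80 % power, each group will need at least 43 participants", then "Assuming that 25 % of patients would be lost to follow-up, each group would need 54 patients, with 162 participants in total".
- **Outcomes** defines the primary outcome as a change: "The primary outcome will be a change in the eating behavior (TFEQ-21, Rep (eat)-Q, and BES) at all steps".
- **Assessment** collects the same electronic form at T0 (before), T1 (immediately after the intervention) and T2 (six months).
- **Analyses plan** compares groups on the initial and final scale values by paired and unpaired t-tests or Mann-Whitney U. It adds: "Differences between the initial and final means (Δ) of the study variables will be calculated". These differences go to an independent-samples t-test or Mann-Whitney U. It also states: "The number needed to treat (NNT) and the number needed to harm (NNH) will be calculated".
- On the analysis set, the same section first offers intention-to-treat, per-protocol or both, and later describes a per-protocol procedure that rests on intention-to-treat. Its only wording on missing data restricts the later regression (mediation) analyses to complete cases.

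**The concern.** A change score needs a final value. A participant without the final form has no Δ and cannot enter a t or Mann-Whitney test on Δ unless a value is supplied by some rule. The article states none for this comparison. Intention-to-treat then governs which arm a participant is counted in, but not whether the participant is counted at all.

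A comparison of completers is sound when loss is unrelated to response, and under the null also when loss depends on response in the same way in each arm. The article gives reasons to doubt that the arms will lose people alike. The program arms attend eight weekly sessions of about two hours or more with home practice, while controls attend two workshops. Controls are also promised the better program after the six-month assessment, which is a reason to stay that program participants do not have. All outcomes are self-completed online.

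At stake are the estimated program effect, the stated 5% error rate, and the choice of program to offer controls, which depends on which one appears more effective.

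**Working it through.** **1. The plan's own figure.** Inputs from Sample size: 30% versus 5%, two-sided 5%, 80% power. Reading the percentages as proportions improved is an assumption, because the article gives no SD and no responder definition.

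- Uncorrected: n = [1.96·√(2·0.175·0.825) + 0.842·√(0.30·0.70 + 0.05·0.95)]² / 0.25² = 35.1, so 36.
- With continuity correction: n = (35.1/4)·[1 + √(1 + 4/(35.1·0.25))]² = 42.7, so **43**, as stated.
- Allowance for loss: 43 × 1.25 = 53.75, so **54**, as stated, and 3 × 54 = 162.

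**2. Who remains.** 54 × 0.75 = 40.5 per arm, so 13 to 14 per arm, or about 40 of 162 (0.25 × 162 = 40.5), have no final value. (Dividing by 0.75 would give 58 per group. That is a separate matter.)

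**3. Size of the bias under assumed loss.** The article does not describe how loss arises, so the patterns below are assumptions, all with no true difference between arms.

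*Simple patterns* (54 per arm, 25% lost in each, t-test on Δ, 10,000 runs, in SDs of the change score):

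| Program arm | Control arm | Bias | Type I error |
|---|---|---|---|
| random | random | 0.00 | 4.9% |
| 40% of below-average changers lost, 10% of others | random | +0.16 | 11.5% |
| worst 25% lost (extreme) | random | +0.42 | 57% |
| 40% / 10% | 40% / 10% | about 0 | 5.2% |

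Check of row 2: the mean of a half-normal is 0.798, so the retained mean is 0.798 × (0.5·0.90 − 0.5·0.60)/0.75 = 0.16. Check of row 3: the normal density at the lower quartile is 0.318, and 0.318/0.75 = 0.42.

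*Three-visit simulation* (54 per arm, within-person correlation 0.6, about 25% lost between T1 and T2, random loss in controls, program-arm loss rising with poor T1 change at a logit slope of 0.75 to 1.5 per SD, in SDs of the scale score). The final value is taken at T2.

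- Completer Δ t-test: bias about 0.08 to 0.12 SD, type I error about 6.5% to 10%.
- Estimate using everyone's T0 and T1 data (likelihood-type): bias 0.00, with about the same SE.
- Same loss pattern in both arms: bias 0.00, type I error about 5%.
- Same selection in the program arm, but T1 also missing for the lost: completer bias 0.08 to 0.125 SD. The likelihood-type estimate is still biased by 0.05 to 0.08 SD.

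**4. Number needed to treat.** Again reading 30% and 5% as proportions improved:

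- completers: 1/(0.30 − 0.05) = 4.0
- lost counted as not improved, 25% random loss in each arm: 1/(0.225 − 0.0375) = 5.3

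The figure therefore depends on the denominator, which the article does not give.

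**The case against.** The strongest reply is that handling of missing values usually belongs in the statistical analysis plan, and that a condensed article leaves out more still. Baseline carried forward or multiple imputation would supply a Δ that the same t-test could take. The authors wrote complete cases for the regressions only, which may mean they intended something else for the group comparison. This has weight: the article does not say that the lost are excluded. But it does fix the test and its data, it expects a quarter of the sample to be lost, and it enlarges the sample so that enough remain. As written, the comparison rests on those with final data. A mixed model would replace the stated method and not merely fill in a detail.

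Two stronger readings are tempting, and the objection is right against both.

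- A reader might infer that the planned analysis favours the programs. The article does not support this. The illustrated direction comes from putting response-related loss in the program arm only. The same pattern in both arms removes the bias, and response-related loss among controls alone would reverse it. Recruitment also plans interaction groups in all three arms and individual contact after a missed session or workshop.
- A reader might infer that the T1 scores go unused. That holds only if the final value means T2. The article does not say which visit is final, and it sets the primary outcome at all steps.

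The trial is also presented as preliminary, which limits the consequences but does not make the estimates any less sensitive to loss.

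**Conclusion.** The concern holds in a conditional form. Absent any stated imputation, the planned between-group tests use only participants with the final form, about three quarters of those randomised, despite the intention-to-treat wording. The result is biased if loss is related to response and differs between arms, and the direction cannot be known beforehand. Under the assumed pattern (response-related loss after T1 in a program arm only, random loss in controls, correlation 0.6) the bias is about 0.08 to 0.12 SD and type I error about 6.5% to 10%. Under random loss, or the same pattern in both arms, there is none under the null.

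Two further inferences go too far. A mixed model does not remove the bias in every case: it does so here when the lost have a T1 score that explains their loss, and only reduces it when they leave before T1. Nor does an intention-to-treat principle oblige the number needed to treat to count the lost as failures. Under random loss 4.0 is the unbiased figure and 5.3 is not, and the article defines no responder.

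**What to change.** In the Analyses plan:

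1. Make the primary between-group comparison of the eating-behaviour scales a likelihood-based mixed model on all randomised participants with any assessment (T0, T1, T2), with the contrast at a named time point.
2. Add one sensitivity analysis in which lost program participants are assumed to follow the workshop arm. It is needed because the mixed model reduces but does not remove bias when loss occurs before T1.
3. Report the number needed to treat with its denominator, and give the version that counts the lost as not improved only as a sensitivity figure.

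The cost is a change of wording and modest extra work in SPSS. No new participants, visits or measurements are needed.

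### Arms are compared by unadjusted tests on final scores and again on raw change, so the baseline score collected from everyone is never used as a covariate

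*Protocol article*

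**What the plan says.** The protocol article has "random allocation in three groups", and every participant completes the same scales at T0, T1 and T2 (Assessment). The primary outcome is change in eating behaviour on three questionnaires: TFEQ-R21, Rep(eat)-Q and BES (Outcomes).

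The Analyses plan section then fixes how arms are compared:

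- At baseline, balance is inspected by eye and also tested. The wording is "For initial comparisons between the groups, the unpaired" version of the t-test or the Mann-Whitney test for continuous variables, and Fisher's exact or chi-square test for categorical ones.
- For the post-intervention data the plan has "a within- and between-group comparative analysis of the scales will be performed with initial and final data using the paired and unpaired" forms of the t-test, with the Mann-Whitney test where data are not normal.
- In addition, "Differences between the initial and final means (Δ) of the study variables will be calculated and a comparative analysis of these means" follows, by independent-samples t-test or Mann-Whitney test.
- For every test, "The level of significance will be 5" per cent.

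The only regression planned in Phase 2 looks at mediation among the scales in the intervention group. It does not compare arms.

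**The concern.** The T0 score is likely to be among the strongest predictors of the later score on the same questionnaire, and it costs nothing extra to use. The final-score test ignores it, so a chance difference between arms at T0 carries through to the result. The change-score test subtracts it in full, which fixes the slope at 1. When the true slope is below 1, this over-corrects and pushes the result the other way.

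Two things are at stake. Arms of this size give wider intervals and usually less power than the collected data allow. The two tests can also disagree on the same scale only because of luck at T0, and no rule says which to believe. That matters in practice, because the control group is later offered whichever programme is judged more effective on eating behaviour (Assessment).

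**Working it through.** **Inputs from the protocol article**

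- Two-sided 5% level, 80% power, 43 per group before losses: "with a 95 % bilateral confidence interval and 80 % power, each group will need at least 43 participants".
- Losses and recruited number: "Assuming that 25 % of patients would be lost to follow-up, each group would need 54 patients, with 162 participants in total". Expected completers are 54 × 0.75 = 40.5, so about 40 per arm.

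**Assumptions (not in the document)**

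- The correlation r between T0 and follow-up scores is taken over 0.3 to 0.8, with the same SD at both times.
- The true difference between two arms is 0.5 SD, for illustration.

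**The plan's own figure.** The 43 per group reproduces if the 30% and 5% improvements are read as two proportions, with pooled variance and continuity correction: 35.06 uncorrected, 42.7 corrected, rounded up to 43. It therefore says nothing about the SD of a scale or about r, and cannot show which analysis of scores has adequate power.

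**Residual variance, as a multiple of the score variance**

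- Final score: 1
- Change score: 2(1 − r)
- ANCOVA: 1 − r²

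Since 1 − r² is below 1 unless r = 0, and 2(1 − r) − (1 − r²) = (1 − r)² is above 0 unless r = 1, ANCOVA is never less precise than either stated test, apart from the one degree of freedom spent on the slope.

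**Power with 40 per arm and a 0.5 SD difference** (noncentral t, with the difference divided by the square root of variance × 2/40)

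| r | Variance: final / change / ANCOVA | Power: final / change / ANCOVA |
|---|---|---|
| 0.3 | 1 / 1.40 / 0.91 | 60% / 46% / 64% |
| 0.5 | 1 / 1.00 / 0.75 | 60% / 60% / 72% |
| 0.7 | 1 / 0.60 / 0.51 | 60% / 81% / 87% |
| 0.8 | 1 / 0.40 / 0.36 | 60% / 94% / 96% |

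The sample-size saving from ANCOVA against the better of the two stated tests is 9% at r = 0.3, 25% at r = 0.5, 15% at r = 0.7 (1 − 0.51/0.60) and 10% at r = 0.8 (1 − 0.36/0.40). Against the worse test it is 35% at r = 0.3 (1 − 0.91/1.40) and 49% at r = 0.7 (1 − 0.51).

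**At the planned 43 per arm.** An unadjusted final-score test has 80% power for 0.604 SD. To detect that difference with 80% power, the number per arm for final / change / ANCOVA is 43 / 61 / 40 at r = 0.3, 43 / 43 / 33 at r = 0.5 and 43 / 26 / 22 at r = 0.7.

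**Chance imbalance.** The T0 difference between two arms of 40 has SD √(2/40) = 0.22 in score SD units. A difference above 0.2 SD arises in about 37% of pairs of arms (35% at 43 per arm). Given an imbalance b, the final-score contrast shifts by r·b and the change contrast by −(1 − r)·b. With r = 0.5 and b = 0.22, these are +0.11 and −0.11 SD. ANCOVA removes the shift.

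**Two tests of one contrast.** With no effect, the two test statistics have correlation √((1 − r)/2). The probability that at least one is significant at 5% is 8.8% at r = 0.3, 9.1% at r = 0.5 and 9.5% at r = 0.8. A simulation at 43 per arm gave 8.7% to 9.3%, with each test alone close to 5%.

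**Skewed scores.** A simulation with gamma-shaped scores, 40 per arm and a 0.5 SD difference gave 60 / 59 / 71% at r = 0.5 and 61 / 78 / 85% at r = 0.7 for final / change / ANCOVA. The advantage does not depend on normality.

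**The case against.** The best defence has four parts.

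1. **Nothing here is invalid.** Under randomisation both stated tests are unbiased on average and each holds its 5% level. This stands: the loss is in precision and in protection from an unlucky T0 draw, not in validity.
2. **The change score does use the baseline, and the primary outcome is worded as a change.** It uses the baseline with a slope fixed at 1, which is not the same as adjusting for it. The wording of the outcome suggests that the Δ test might lead, but the Analyses plan still lists both tests at the same level and ranks neither. The 9% figure applies only if a significant result on either test would be taken as a finding, which the plan does not rule out.
3. **The gain peaks at r = 0.5.** This is correct. Against the better stated test it is 4 points of power at r = 0.3, 6 at r = 0.7 and 2 at r = 0.8. But the better test depends on r: final scores below 0.5, change above. The document gives no r by which to choose in advance, and ANCOVA removes the need.
4. **This is a feasibility study reported in a condensed article.** The article still sizes the trial for 80% power and hypothesises that one programme is superior. It also names the tests, so this is a stated method rather than a detail left to an analysis plan not shown.

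**Conclusion.** The concern holds. The stated analysis compares arms twice per scale, without a baseline covariate and without saying which result leads. With about 40 completers per arm and a 0.5 SD difference, ANCOVA adds 2 to 12 percentage points of power over the better stated test for r between 0.3 and 0.8, and up to 36 points over the worse one (60% against 96% at r = 0.8). The two stated tests respond in opposite directions to a chance T0 imbalance, and together carry a false-positive rate of about 9% per scale and pair of arms.

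These sizes rest on the assumed r, equal SDs over time and the illustrative effect. The direction does not depend on the particular r or effect chosen. The point should be fixed, though it does not invalidate the trial.

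**What to change.** In the Analyses plan, replace both between-arm tests, for each scale and for weight, with one linear model over the three arms at each follow-up time: follow-up score on arm plus the T0 value of the same score. Report adjusted mean differences between arms with 95% confidence intervals.

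Drop the final-score and Δ two-sample tests as analyses of effect. Drop the baseline significance tests as well, and keep the descriptive baseline table.

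This gives one answer per scale, time and pair of arms. It does not settle which questionnaire, time point or contrast is the main one; that needs its own statement.

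The cost is wording only. No new data or participants are needed, and the model runs in the SPSS version already named.
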